#### Twelve months postoperatively

- Physical examination, including circumferential measurement of both legs at defined landmarks, Lachman and pivot shift tests, KT-1000 arthrometer objectifying of instability, one-legged hop test, Lysholm, Tegner, and IKDC scores, knee and kneeling pain measured by visual analogue scales

- Any complications or complaints raised by the patient, GP/ ambulatory surgeon, or Clinical Investigators

- Resumption of work and leisure activities

- MRI scan according to local standards

### MRI studies

Radiological evaluation comprises

- Tunnel widening

- Impingement

- Transplant sufficiency, morphology of transitional areas and tendon-bone-interfaces

- Degree of degradation of screws and pins

- Degree of inflammation (synovitis) and effusion

- Presence or progression of arthrofibrosis

- Changes in cartilage and meniscal morphology

### Physical examination

Before physical examination, both knees are prepared by applying opaque dressings to hide scars and to blind the examining doctors for the managed side.

Examination is performed independently by two of three board-certified surgeons ([name], [name], [name]) who had not operated on any of the patients in the study. The responsible surgeon ([name]) conducts a third clinical examination after completion of the case report forms. We document his examination findings separately and consider them as the diagnostic reference standard. We assess both interobserver agreement by kappa statistics and the accuracy of measurements taken by independent observers comparing with those of the responsible surgeon.

### KT-1000 arthrometer testing

Objective translation measurements comprise a defined load (89 N). We measure the anterior translation of the injured and healthy side (in mm), as well as the difference between both knees.

### Safety assessment and reporting of adverse event

We define an adverse event as 'any undesirable clinical instance in a subject whether it is considered treatment related or not'. In addition, an adverse device effect, undesirable side effect, is defined as 'a device related adverse event'.

A record of all adverse events, including details of the nature, onset, duration, severity, relationship to the device, relationship to the operative procedure and outcome, will be made on the relevant section of the subject's CRF. The subject will be questioned about any adverse event at each later follow-up assessment visit.

An adverse event or an adverse device effect may be mild, moderate or severe and are usually unexpected.

A severe adverse event or adverse device effect is defined as any experience that

- is fatal or life-threatening

- is permanently disabling

- needs or prolongs in-patient hospitalization because of a potential disability, danger to life or forces an intervention

All severe adverse events or adverse effects which occur during this investigation must be and will be reported immediately by telephone or facsimile to

Bundesinstitut für Arzneimittel und Medizinprodukte, [name], Phone: +[contact], Fax: +[contact]

### Data management

For data collection, we set up a Microsoft XP Professional Access^® ^Database, run on a mobile computer separately from the hospital documentation and the intranet. Data collection and storage comply with orders fixed by the data safety board of the Unfallkrankenhaus Berlin, and follow German laws for data safeguard and protection (*Bundesgesetz über den Schutz personenbezogener Daten *[Datenschutzgesetz 2000 – DSG 2000], 17. August 1999, BGBl. I Nr. 1999/165). We ensure data storage for five years.

For study documentation, we assign patients an identification number. Electronic sources do not contain names or addresses of participants. Linking lists are stored in a study folder with copies of adverse events forms.

Since this study runs at a single centre, we do not appoint an external monitor for data handling and management. We regularly (at least twice a month) check datasets for consistency, completeness and plausibility.

### Statistical analysis

We will conduct all analyses following the intention to treat principle (that is, patients will be evaluated as randomized).

We will express measurements as means, medians or proportions with their proper distribution indices (that is, standard deviations, ranges, and interquartile ranges). In case of skewed distributions, normalizing will be achieved by logarithmic transformation, where necessary.

As pointed out earlier, we will address only the primary hypothesis in a confirmatory fashion, whereas all other results will be evaluated in a plain exploratory intent.

We will employ the student's t-test for independent samples to test for the difference in anterior laxity between both fixation methods at six months of follow-up.

For secondary endpoint analysis, we will calculate cross tables, 95% confidence intervals for normally or binomially distributed data, and differences in means, proportions, and ratios. In case of obvious benefits or harms with either device in a certain subgroup of patients, we will use stratified analyses (for example, according to Mantel-Haenszel).

Where statistically and/ or clinically sound, we will consider linear and logistic regression analyses, or more sophisticated regression models for correlated data (for example, generalized estimating equations). We will, however, respect the small sample size of this study, and limit statistical analyses to the necessary minimum.

In case of missing data, we will use both a last observation carried forward approach, and imputation methods by regression or semi-Bayesian modelling. Separate analyses will be performed for raw and modelled data.

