**Design/ Methods:**

SPOT is a randomised, controlled, patient and investigator blinded trial conducted at a single academic institution. Eligible patients are scheduled to arthroscopic ACL repair with triple-stranded hamstring grafts, conducted by a single, experienced surgeon. Intraoperatively, subjects willing to engage in this study will be randomised to transplant tethering with either resorbable screws or resorbable pins. No other changes apply to locally established treatment protocols. Patients and clinical investigators will remain blinded to the assigned fixation method until the six-month follow-up examination.

The primary outcome is the side-to-side (repaired to healthy knee) difference in anterior translation as measured by the KT-1000 arthrometer at a defined load (89 N) six months after surgery. A sample size of 54 patients will yield a power of 80% to detect a difference of 1.0 mm ± standard deviation 1.2 mm at a two-sided alpha of 5% with a t-test for independent samples.

Secondary outcomes (generic and disease-specific measures of quality of life, magnetic resonance imaging morphology of transplants and devices) will be handled in an exploratory fashion.

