### Primary endpoint

We pose the primary hypothesis that the RigidFix^® ^system preserves graft tension gained during surgery, and leads to lower KT-1000 arthrometer side-to-side differences than the BioCryl^® ^screw after six months of follow-up.

Specifically, we will test the hypothesis that RigidFix^® ^decreases the average difference gained with interference screws by 1.0 ± standard deviation 1.2 mm. The investigators consider this difference clinically sound, important, and measurable by KT-1000 arthrometer testing. Twenty-four subjects a treatment arm will allow for detecting this difference with an 80% chance at a two-sided alpha-level of 5%. Assuming a drop-out rate of 10%, 54 patients will be enrolled in this study.

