### Baseline assessment

Each subject considered eligible for entry into this investigation has the following information and procedures recorded at the pre-investigational examination:

- Demographic details including date of birth and gender

- Medical history, coexisting diseases, and accompanying medication

- Physical examination, including circumferential measurement of both legs at defined landmarks, Lachman and pivot shift tests, KT-1000 arthrometer objectifying of instability, one-legged hop test, Lysholm, Tegner, and IKDC scores, knee and kneeling pain measured by visual analogue scales

- Radiographic examination, including a conventional roentgenogram of the injured knee in anteroposterior and lateral projection, and a preoperative MRI scan according to local standards

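### The confirmatory t-test leaves the pre-operative KT-1000 value unused: a valid test, but a missed efficiency that one prespecified covariate could recover

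*Protocol article*

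**What the plan says.** The abstract of the protocol article defines the endpoint: "The primary outcome is the side-to-side (repaired to healthy knee) difference in anterior translation as measured by the KT-1000 arthrometer" at 89 N, six months after surgery. The Primary endpoint section sets the target, namely that pinning "decreases the average difference gained with interference screws by 1.0 ± standard deviation 1.2 mm", and the size: "Twenty-four subjects a treatment arm will allow for detecting this difference with an 80% chance at a two-sided alpha-level of 5" percent, then "Assuming a drop-out rate of 10%, 54 patients will be enrolled in this study". The abstract bases this calculation on a t-test for independent samples. The Statistical analysis section names the same test for the six-month comparison, "We will employ the student's t-test for independent samples to test for the difference in anterior laxity between both fixation methods", and attaches no covariate to it.

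The Baseline assessment section lists "KT-1000 arthrometer objectifying of instability" among the procedures recorded for each subject considered eligible. The KT-1000 arthrometer testing section says that both knees and their difference are measured. Read together, these mean that the pre-operative side-to-side difference will be available on the same scale as the outcome.

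Regression appears only as something the authors may consider where sound. That statement follows the secondary-endpoint analyses and is tied neither to the primary endpoint nor to a baseline covariate. The Design section describes blocked randomisation and states no stratification.

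**The concern.** A baseline measurement of the outcome itself is planned for every patient, but the confirmatory comparison ignores it. In a trial of this size two things are at stake. If the baseline value predicts the six-month value, adjusting for it narrows the confidence interval around the same difference in mm, in a design with almost no power in reserve. Also, with about 24 patients per arm and no stratification, the arms can differ by chance in pre-operative laxity, and the unadjusted estimate then carries part of that difference.

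Timing also matters. If an imbalance is seen, the open wording on regression would leave any adjusted analysis to be chosen after the data are known. Naming the covariate beforehand closes that choice.

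**Working it through.** **Inputs from the article.** Difference 1.0 mm, SD 1.2 mm, two-sided 5%, 24 evaluable per arm, 10% drop-out, 54 enrolled. Equal allocation is inferred from the 24 per arm.

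**Assumed input.** The correlation r between the pre-operative and six-month side-to-side differences is not given, so a range from 0 to 0.5 is shown.

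**1. The plan's own figure.** The standard error of the unadjusted difference is 1.2 × √(2/24) = 0.346 mm, so the noncentrality is 1.0/0.346 = 2.887. The noncentral t with 46 degrees of freedom gives 80.7% power; 23 per arm gives 78.9%. So 24 per arm is the smallest sufficient number, and 48/0.9 = 53.3, which becomes 54 for two equal arms. The stated sample size reproduces.

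**2. Power after adjustment.** With N = 48, the adjusted analysis has residual SD 1.2 × √(1 − r²). Estimating the slope multiplies the variance by 1 + 1/(N − 4) = 45/44 = 1.023, and N − 3 = 45 degrees of freedom remain. Noncentrality = 1.0 / [1.2 × √(1 − r²) × √(45/44) × √(2/24)].

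| r (assumed) | Variance relative to t-test | 95% CI half-width (mm) | Power |
|---|---|---|---|
| t-test | 1 | 0.697 | 80.7% |
| 0 | 1.023 | 0.706 | 79.8% |
| 0.2 | 0.982 | 0.691 | 81.3% |
| 0.3 | 0.931 | 0.673 | 83.3% |
| 0.4 | 0.859 | 0.647 | 86.2% |
| 0.5 | 0.767 | 0.611 | 89.7% |

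**3. Break-even.** The variances are equal when (1 − r²) × 45/44 = 1, so r² = 1/45 and r = 0.149. Below that, adjustment costs a little; at r = 0 the cost is 80.7 − 79.8 = 0.9 percentage points.

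**4. Chance imbalance.** In SD units, the baseline difference between two randomised arms of 24 has standard deviation √(2/24) = 0.289.

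- Chance of exceeding 0.3 SD in either direction: 2 × [1 − Φ(0.3/0.289)] = 30%.
- Chance of exceeding 0.5 SD: 2 × [1 − Φ(0.5/0.289)] = 8%.

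An imbalance of d SD shifts the expected unadjusted estimate by d × r × 1.2 mm. For d = 0.5 this is 0.5 × 0.3 × 1.2 = 0.18 mm at r = 0.3, and 0.5 × 0.5 × 1.2 = 0.30 mm at r = 0.5, against a target of 1.0 mm. At r = 0 the shift is zero. Steps 2 and 4 show the same benefit, first averaged over possible randomisations and then within one unlucky randomisation, so they should not be added together.

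**The case against.** The strongest reply is that nothing here is wrong. The t-test is prespecified, valid under randomisation, and the test for which the trial was sized. Its standard error and 5% error rate already allow for chance imbalance. All of this stands. A reader might infer that the planned test is biased or the trial underpowered; the article supports neither.

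A second objection is that a useful correlation cannot be presumed. Subjects have a first total or subtotal rupture, and surgery replaces that ligament with a tensioned hamstring graft. The baseline reading mainly describes the torn ligament, whereas the outcome describes the graft and its fixation. This is not one structure measured twice, and r may be low. This also stands. A reader might infer that adjustment will certainly improve precision, or that fewer patients would do. Without a stated correlation, neither follows: at r = 0.2 the gain is only 0.6 points, and below about 0.15 there is a slight loss.

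A third objection is that the authors keep regression available and wish to limit analyses because the sample is small. That would accommodate a supportive adjusted analysis, but it does not alter the stated confirmatory test. One model with one covariate is also compatible with their restraint.

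**Conclusion.** The point holds as a recommended improvement, not as a validity flaw. The article commits the confirmatory test to an unadjusted comparison while planning to collect the baseline value of the same measure in every eligible subject.

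The size of the gain rests on r, which is assumed: under three points of power at r = 0.3, nine points at r = 0.5, and a loss of about one point at r = 0. All figures also assume the planned SD of 1.2 mm, equal arms of 24 evaluable patients, a linear relation between baseline and outcome, and normally distributed residuals. The case is one of a small, bounded cost against a possible material gain, together with an estimate corrected for chance baseline imbalance by a rule set in advance.

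**What to change.** In the Statistical analysis section, make the confirmatory test the treatment coefficient, with its 95% confidence interval, from an analysis of covariance of the six-month KT-1000 side-to-side difference (mm) on treatment arm and the pre-operative side-to-side difference, at two-sided 5%. Keep the independent-samples t-test as a supportive analysis. State that the covariate was chosen in advance and is used whether or not the arms look balanced.

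Leave enrolment at 54, since no correlation is available to justify a smaller number. The quantity estimated, the between-arm mean difference in mm, is unchanged.

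The cost is a sentence or two before the analysis. No new data are needed, and at worst about one percentage point of power is given up.

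### The exploratory subgroup rule is triggered by the result itself, and its one named method can dilute or hide the subgroup difference that triggered it

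*Protocol article*

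**What the plan says.** The rule stands in the secondary-endpoint paragraph of the Statistical analysis section. That paragraph opens: "For secondary endpoint analysis, we will calculate cross tables, 95% confidence intervals for normally or binomially distributed data". It then sets the condition for looking at subgroups, "In case of obvious benefits or harms with either device in a certain subgroup of patients, we will use stratified analyses", and gives Mantel-Haenszel in brackets as an example of how this would be done. No subgroup is named, nothing says what counts as obvious, and no test or estimate of a difference between subgroups is mentioned.

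Three neighbouring statements bear on the rule:

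- On inferential status: "we will address only the primary hypothesis in a confirmatory fashion, whereas all other results will be evaluated in a plain exploratory intent".
- On further models: "we will consider linear and logistic regression analyses, or more sophisticated regression models for correlated data". Interaction terms are not mentioned.
- On restraint: the plan will "respect the small sample size of this study, and limit statistical analyses to the necessary minimum".

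**The concern.** There are two linked problems, both in what the sentence states rather than in what it leaves out.

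First, the decision to analyse a subgroup depends on that subgroup's result. A subgroup enters the report because its effect looked large, so its estimate is biased away from zero by selection, and a reader cannot count how many subgroups were looked at.

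Second, the example method answers a different question from the one that the trigger raises. The trigger is an apparent effect in one part of the sample. The natural next question is whether the device effect really differs between that part and the rest. A Mantel-Haenszel common estimate adjusts for strata and returns one averaged effect. It neither tests nor estimates a difference between strata, and is easiest to interpret when there is none.

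At stake is how the exploratory results can be read: a chance subgroup finding could be reported, or a real difference diluted, with nothing in the stated method to tell the two apart.

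**Working it through.** **Sample size, reproduced first.** Inputs from the Primary endpoint section: difference 1.0 mm, SD 1.2 mm, two-sided alpha 5%, power 80%, drop-out 10%.

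- Normal approximation: n per arm = 2 × (1.960 + 0.842)² × 1.2² / 1.0² = 22.6, so 23.
- t-test (noncentral t): 23.6, so 24 per arm, with power 80.7%.
- Drop-out: 48 / 0.90 = 53.3, so 54.

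The stated 24 per arm and 54 enrolled are reproduced. The checks below use 48 evaluable patients.

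**What a Mantel-Haenszel estimate does with unequal strata.** Illustrative tables, 12 per arm per stratum. With a, b the events and non-events in one arm, c, d those in the other, and N = 24 per stratum, the common odds ratio is Σ(ad/N) / Σ(bc/N).

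| Stratum 1 | Stratum 2 | Stratum odds ratios | Common odds ratio |
|---|---|---|---|
| 10/12 vs 4/12 | 6/12 vs 6/12 | 10 and 1 | (80 + 36)/(8 + 36) = 2.64 |
| 8/12 vs 4/12 | 6/12 vs 6/12 | 4 and 1 | (64 + 36)/(16 + 36) = 1.92 |
| 8/12 vs 4/12 | 4/12 vs 8/12 | 4 and 0.25 | (64 + 16)/(16 + 64) = 1.00 |

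In the first two rows, the effect that would have triggered the analysis is diluted. In the third, it disappears.

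**How often chance alone would trigger the rule.** The article gives neither the number of factors nor a threshold. Assumed: balanced binary factors (12 per arm in each level), one normally distributed outcome at one visit, no device effect anywhere. Two possible triggers were tried: p<0.05 in a subgroup t-test, and an observed difference of at least 1.0 mm, the trial's own target effect, with SD 1.2 mm. Simulation of 10,000 trials for each number of factors:

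| Factors (subgroups) | Any subgroup p<0.05 | Any subgroup difference ≥1.0 mm |
|---|---|---|
| 1 (2) | 9.8% | 8.3% |
| 3 (6) | 21.5% | 17.8% |
| 5 (10) | 28.9% | 23.3% |

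The first row agrees with 1 − 0.95² = 9.75%. For 3 and 5 factors the independence formula would give 1 − 0.95⁶ = 26.5% and 1 − 0.95¹⁰ = 40.1%. These are too high, because the same patients sit in subgroups of several factors.

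**What an interaction estimate could show.** With 12 per cell and SD 1.2 mm, the standard error of the difference between two subgroup effects is 1.2 × √(4/12) = 0.69 mm. With 44 degrees of freedom and two-sided 5%, power is about 29% for an interaction of 1.0 mm and about 81% for 2.0 mm. An uneven factor does worse: with 18 and 6 per arm in the two levels, the standard error is 1.2 × √(2/18 + 2/6) = 0.80 mm.

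**The case against.** The case on the other side is substantial, and most of it stands as a limit on the point.

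- **The method is an example.** The text reads "we will use stratified analyses (for example, according to Mantel-Haenszel", so what is prescribed is stratified analysis, which ordinarily shows each stratum's result, and regression models are also allowed. A reader might infer that the plan commits itself to pooling and so averages real differences away. The text does not support that; it supports only that the one method named can do so.
- **The Mantel-Haenszel test is not invalid.** Similar effects across strata are needed to interpret the common estimate. The test keeps its level when there is no effect in any stratum.
- **Mantel-Haenszel suits some of these outcomes.** A reader might object that it is a method for binary data. But the same paragraph plans cross tables, and the trial records categorical findings such as pivot shift, return to work and MRI signs. That objection fails.
- **The consequence is bounded.** A reader might infer a threat to the trial's error rate. The rule sits under secondary endpoints, everything there is exploratory, and the primary analysis is an unstratified t-test.
- **Subgroup lists often belong in an analysis plan that is not shown.** That is so, and their absence here is no finding. The stated trigger and the example are a different matter, because the article does fix those.
- **The promise to "limit statistical analyses to the necessary minimum" restrains searching.** It is a general caution about sample size. It does not say which subgroups may be looked at, and it does not change a trigger that depends on the result.

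The exploratory label limits what may be claimed. It does not match the example method to the question, and it does not make a subgroup chosen by its result informative.

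**Conclusion.** The point holds in a limited form. The stated rule selects subgroups by their results, and its only named example gives a common estimate that can dilute or hide the difference in question and does not assess effect modification. The pooled odds ratios are exact for the illustrative tables; they are not predictions for this trial. The 10% to 29% range rests on an assumed 1 to 5 balanced binary factors, one outcome and a p<0.05 trigger. Looking across several outcomes and the visits at 3, 6 and 12 months would give more opportunities. The figures in mm use the KT-1000 SD from the sample size section and are only a scale for illustration, since the rule concerns secondary endpoints. The primary comparison, its alpha and the sample size are unaffected. This is a low-priority correction to exploratory analyses.

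**What to change.** Replace the sentence with wording such as: 'Subgroup effects will be examined for a short list of factors fixed before unblinding (for example sex, total or subtotal rupture, meniscal procedure). For each, stratum-specific estimates and a treatment-by-subgroup interaction estimate from a linear or logistic model will be reported with 95% confidence intervals, whatever the result. Any other subgroup signal, including unexpected harm, will be labelled post hoc and described only. Mantel-Haenszel methods will be used only to adjust categorical outcomes by strata fixed in advance.'

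Because patients and examiners may learn the allocation one by one once each six-month form is complete, the list should be fixed before the first such form is completed. The plan should also say that interaction power is low, giving the 29% and 81% above with their assumptions.

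The cost is a short replacement text and a few model terms, with no change in sample size. The downside is that subgroups not listed in advance can only be described, and that most interaction estimates will be imprecise.

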### Secondary endpoints

As secondary endpoints, we consider functional outcomes by means of the Lysholm scale, the Tegner score, and the International Knee Documentation Committee evaluation form (IKDC) in its German translation, 2000 revision [18]. Besides disease-specific items, this questionnaire also contains the Short-Form 36 (SF-36) generic health assessment tool. The noted instruments have proven reliability, validity, and responsiveness for use in clinical research.

Confirmatory testing will apply for the primary endpoint only. All secondary endpoints will be addressed in an exploratory fashion.

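### Three missing-data treatments of the sole confirmatory test have no stated order of precedence, and last observation carried forward could enter a pre-operative reading as the six-month result

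*Protocol article*

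**What the plan says.** The Statistical analysis section names one test for the primary outcome: "We will employ the student's t-test for independent samples to test for the difference in anterior laxity between both fixation methods at six months of" (quote cut before its last word). The Secondary endpoints section makes it the only confirmatory one: "Confirmatory testing will apply for the primary endpoint only".

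The missing-data rule, also under Statistical analysis, has two parts. First: "In case of missing data, we will use both a last observation carried forward approach, and imputation methods by regression or semi-Bayesian modelling". Then: "Separate analyses will be performed for raw and modelled data". Neither sentence is limited to secondary outcomes, and neither ranks the resulting analyses. The intention-to-treat sentence in the same section settles which group a patient is analysed in. It does not settle how a missing value is treated.

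On loss to follow-up, the Primary endpoint section says: "Assuming a drop-out rate of 10%, 54 patients will be enrolled in this study".

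KT-1000 laxity is recorded before surgery (Baseline assessment) and at 3, 6 and 12 months (Follow-up assessments). Only one post-operative reading therefore precedes the primary time point.

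**The concern.** There are two separate problems.

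**No deciding analysis.** Raw, carried-forward and model-imputed data give at least three p-values for one hypothesis. The choice between regression and semi-Bayesian modelling is open as well, and the text does not say whether imputation is single or multiple. If the results disagree around 0.05, the protocol gives no rule for the conclusion.

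**What is carried forward.** A patient who misses only month 6 receives the month-3 value. This assumes that laxity does not change afterwards, although the hypothesis is about whether fixation preserves graft tension up to six months. A patient who misses both visits has only the pre-operative reading left, taken on an injured, unrepaired knee. Nothing in the text prevents that reading from standing as the result of surgery. A few such values widen the spread, dilute a real effect, and favour one arm if drop-out is unequal.

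**Working it through.** **Inputs from the protocol.** Two-sided alpha 5%, power 80%, "Twenty-four subjects a treatment arm", and an effect such that pinning "decreases the average difference gained with interference screws by 1.0 ± standard deviation 1.2 mm" (Primary endpoint). Drop-out 10%, 54 enrolled. Residual laxity after hamstring grafting 2.28 mm (Background), used here as the control mean, so the pin mean is 2.28 − 1.0 = 1.28 mm.

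**Assumptions not in the protocol.** 27 per arm; pre-operative side-to-side difference 6 mm, SD 2 (range 4 to 8 mm); month 3-to-6 correlation 0.6; correlation with baseline 0.3; equal means and effect at months 3 and 6; values missing at random with respect to laxity. Let q be the share of patients with a missing six-month value who also lack month 3, and so carry baseline.

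**1. The plan's own figure.** Standardised effect 1.0/1.2 = 0.833. The noncentral t calculation gives 23.6, so 24 per arm, with 80.7% power. Then 48/0.9 = 53.3, so 54. The sample size reproduces, and it already covers 10% loss without any filling-in.

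**2. Power under last observation carried forward, 10% missing in each arm.** The fraction of an arm carrying baseline is w = 0.10q. The expected contrast is (1 − w) × 1.0 mm. The variance in an arm with mean μ is (1 − w)·1.2² + w·2² + w(1 − w)(6 − μ)².

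- q = 0: contrast 1.00, SD 1.20, power with 27 per arm 85%.
- q = 0.5: w = 0.05. Control variance 1.368 + 0.200 + 0.657 = 2.225; pin variance 1.368 + 0.200 + 1.058 = 2.626; pooled SD √2.426 = 1.56. Contrast 0.95, ratio 0.61, power about 60%.
- q = 1: w = 0.10. Variances 2.941 and 3.701; pooled SD √3.321 = 1.82. Contrast 0.90, ratio 0.49, power about 43%.

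The formula treats skewed data as normal. Simulation gives 85 to 86%, 61% and 46%. Observed-case power in the same simulations is 80 to 82%. At q = 0.5, simulated power under carry-forward is 72% for a 4 mm baseline and 50% for 8 mm.

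**3. Bias with 15% against 5% missing, no true effect.** Bias = (0.15 − 0.05) × q × (6 − 2.28) = 0.372q mm, making the arm with more drop-out look laxer.

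| q | Formula | Simulation |
|---|---|---|
| 0 | 0 mm | about 0 mm |
| 0.5 | 0.19 mm | 0.18 mm |
| 1 | 0.37 mm | 0.37 mm |

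For baselines of 4 to 8 mm, q = 0.5 gives 0.1 × 0.5 × 1.72 = 0.09 mm to 0.1 × 0.5 × 5.72 = 0.29 mm.

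**4. Type I error if the analyst may choose, 10% missing in each arm.** Three independent tests would give 1 − 0.95³ = 14.3%. These three are strongly correlated, so the true figure is lower. In simulation the observed-case and carried-forward tests each reject in about 5%, and deterministic regression imputation in about 7%. At least one of the three rejects in about 7% (q = 0), 9% (q = 0.5) and 10% (q = 1). Proper multiple imputation with Rubin's rules rejects in 5.0% on its own.

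**The case against.** The strongest reply is that the ranking of missing-data analyses is ordinary analysis-plan content, that an analysis plan may exist, and that this is a condensed article. The protocol names one test and inflates 48 to 54 for drop-out, which fits an observed-case primary analysis; the separate analyses can then be read as sensitivity reporting. That reading is reasonable, but the text does not state it. The article did not stay silent: it prints a rule that covers the primary endpoint, and the rule is open on the point that matters.

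Other parts of the reply stand, and they rule out stronger readings that a reader might infer:

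- **That the plan uses single imputation.** The text does not say single or multiple. The 7% rejection rate belongs to deterministic imputation only.
- **That the plan's error rate exceeds 5%.** Nowhere does the protocol count significance in any one analysis as success. The 7 to 10% arises only if the best result may be picked.
- **That carrying values forward necessarily costs power.** With only month-3 values carried, power is about 85%, slightly above observed cases, and unequal drop-out produces no bias. This assumes the same means and effect at months 3 and 6.
- **That the carried baseline comes from a knee without a functioning ligament.** The Inclusion criteria admit subtotal ruptures.
- **That the t-test must give way to a mixed model.** The observed-case t-test keeps about 5% error and 80% power when values are missing completely at random, and the protocol promises to keep analyses to the necessary minimum.

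**Conclusion.** The concern holds in this form. The missing-data rule reaches the only confirmatory test, ranks none of its analyses, and permits a pre-operative reading to serve as the six-month outcome.

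The lack of a deciding analysis rests on the text alone. The numerical harm is conditional. Planned loss is 10% of 54, about 5 to 6 patients, and the protocol gives neither how many would miss both visits nor any pre-operative laxity. On the assumptions above, the consequence of carry-forward runs from none (85% power, no bias) to serious (46% power, 0.37 mm bias against a 1.0 mm target under unequal drop-out). This should be fixed before analysis. It does not undermine the design or the sample size.

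**What to change.** Before any look at six-month data by arm, name one primary analysis for the KT-1000 comparison. Either of these would serve:

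- the stated t-test on observed six-month values, noting that it relies on values being missing completely at random; or
- the same comparison after proper multiple imputation from arm, baseline and month-3 KT-1000, combined by Rubin's rules.

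Drop last observation carried forward for the primary endpoint, or at least state that a pre-operative value is never carried into a post-operative visit. Say whether any imputation is single or multiple, and which model is used. Label every other missing-data analysis as a sensitivity analysis that cannot change the confirmatory conclusion.

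The cost is a few sentences and, for multiple imputation, slightly more programming. No new data or patients are needed.
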